### Outcomes measurement

Patients will be assessed five times: before treatment and 1, 3, 6 and 12 months after the treatment (Table 1). The PROMs consist of the four questionnaires: The Knee injury and Osteoarthritis Outcome Score (KOOS) [16–18], International Knee Documentation Commitee 2000 (IKDC 2000) [19, 20], the Western Ontario and McMaster Universities Osteoarthritis Index (WOMAC) [21, 22], the Health Questionnaire EQ- 5D- 5 L [23, 24].

**Table 1 Tab1:** The study procedures schedule

Visit	1	2	3	4	5
Month (m)	0	1 m	3 m	6 m	12 m
Study qualification	X				
Consent form signing	X				
Autologous fat tissue/ PRP intra- articular injection	X				
Questionnaires:					
KOOS	X	X	X	X	X
IKDC 2000	X	X	X	X	X
WOMAC	X	X	X	X	X
EQ-5D-5 L	X	X	X	X	X
Functional tests:					
TUG	X	X	X	X	X
5xSTS	X	X	X	X	X
10mWT	X	X	X	X	X
Strength measurement:					
MVIC	X	X	X	X	X

Moreover, three functional tests will be performed to assess patient’s functional status: The Timed Up and Go Test (TUG) [25], The 5 Times Sit to Stand Test (5xSTS) [26], The 10 m Walk Test (10mWT) [27]. To assess strength parameters of the knee flexors and extensors the Maximal Voluntary Isometric Contraction (MVIC) will be measured. Each test will be supervised by the same one physiotherapist to avoid any interexaminer bias and discrepancies during testing.

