### Ethics, data management and statistical analysis

All procedures used for this study have been approved by Bioethics Committee, Poznan University of Medical Sciences on 16th December 2019 (no. 868/18). The tile of the project accepted by Bioethics Committee: “Prospective functional evaluation of knee osteoarthritis treatment with autologous fragmented adipose tissue and platelet-rich plasma (PRP) – comparison of two different treatment methods”. All patients will be obliged to give written agreement for the participation in the study. Collected data will be stored at the clinic in a database created particularly for this study containing appropriate security features. In database each participant will have a special code to minimize the risk of identification of a given patient. Only patients who attended all of visits, performed each functional test and MVIC and fulfilled each questionnaire will be included in the analysis. The consequence of the absence on a visit will be exclusion from the study. Basic analysis will include descriptive statistics of demographic characteristics to assess both groups homogeneity. Such analysis will be done several times during testing to detect any confounders which may influence the balance between treatment groups. At the start we consider BMI, age, sex and knee OA grade as a possible confounders, but in a further analysis we will also look for any correlations between them and treatment effectiveness. At every time point the results will be compared between treatment and control group, what is main purpose of this study. The results obtained in each questionnaire, functional test and MVIC will create the effect across all time points. A *p*- value of < 0.05 will be considered statistically significant.

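### Correlating BMI, age, sex and OA grade with outcome measures prognosis; it cannot show whether the fat-versus-PRP difference depends on these factors

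*Protocol article*

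**What the plan says.** All the relevant analysis text is in the protocol article, section Ethics, data management and statistical analysis.

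- **Factors.** "At the start we consider BMI, age, sex and knee OA grade as a possible confounders".
- **Planned search.** The same sentence continues: "in a further analysis we will also look for any correlations between them and treatment effectiveness". The article does not define effectiveness, does not say whether the correlations are pooled or by arm, and mentions no treatment-by-covariate interaction.
- **Main purpose.** "At every time point the results will be compared between treatment and control group", and the article calls this comparison the main purpose of the study.
- **Threshold.** One rule covers everything: a p-"value of < 0.05 will be considered statistically significant". The covariate search carries no exploratory label.

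The section Outcomes measurement supplies the rest: "The PROMs consist of the four questionnaires"; "three functional tests will be performed to assess patient’s functional status"; and "To assess strength parameters of the knee flexors and extensors the Maximal Voluntary Isometric Contraction (MVIC) will be measured". Assessments take place "before treatment and 1, 3, 6 and 12 months after the treatment". The Discussion concedes that the study is small, but the article gives no sample size.

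**The concern.** The trial asks whether fat tissue works better than PRP. The natural follow-up is whether that advantage differs by BMI, age, sex or grade. A correlation does not answer it. Each patient has a result under one treatment only, so effectiveness at patient level can only be that patient's score or change. If patients with a lower grade do better on either treatment, grade will correlate with the result even when the fat-minus-PRP difference is the same at every grade.

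Because the wording attaches the correlation to the effectiveness of treatment, a prognostic finding could easily be reported as a treatment-specific one. The reverse error is also possible: a factor that changes the treatment difference may leave no pooled correlation at all. The open scope (any correlation, on any measure, at any visit, at an unadjusted 5%) adds chance findings on top.

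**Working it through.** The article gives no sample size, effect size or variance, so there is no stated figure to reproduce. Two separate checks follow.

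**1. What each method picks up**

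Assumptions, not document figures: 20, 30 or 50 patients per arm, 1:1; one continuous covariate; normal outcome with SD 1 in each arm; two-sided 5% tests. I simulated 100,000 trials per setting. The interaction test is the t-test on the product term in: outcome = a + b·covariate + c·arm + d·(covariate × arm).

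*(a) Purely prognostic factor:* correlation 0.3 in both arms, between-arm difference 0.3 SD, true d = 0.

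| Per arm | Pooled correlation significant | One given arm significant (p) | Exactly one arm significant | Interaction significant |
|---|---|---|---|---|
| 20 | 47% | 25% | 38% | 5% |
| 30 | 64% | 37% | 47% | 5% |
| 50 | 86% | 57% | 49% | 5% |

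The arms are independent, so the fourth column should equal 2p(1 − p), and it does:
- 2 × 0.254 × 0.746 = 0.379
- 2 × 0.367 × 0.633 = 0.465
- 2 × 0.573 × 0.427 = 0.489

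The 47% to 86% is power to find a real prognostic link. It becomes an error only if the result is read as effect modification. The fourth column applies only if the arms are analysed separately and their p-values compared.

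*(b) True effect modifier, extreme case:* correlations +0.4 and −0.4 in the two arms. The pooled correlation is significant in about 7% of trials at every size; the interaction test in 71%, 88% and 98%.

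*(c) Modest effect modifier:* correlations 0.4 and 0.1. The interaction test is significant in only 15%, 21% and 33%.

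So the pooled correlation responds to (a), where the treatment difference does not vary, and misses (b), where it does. The interaction test targets the right quantity but has little power in a realistic case such as (c).

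**2. How many chance findings an open search allows**

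Inputs: 4 factors; 4 questionnaires + 3 functional tests + MVIC as one or two measures (flexors, extensors) = 8 or 9 measures, one score per questionnaire; 4 post-baseline visits; threshold 0.05.

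Expected chance findings if no association exists = tests × 0.05. Chance of at least one, if the tests were independent = 1 − 0.95^tests.

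| Search | Tests | Expected | At least one |
|---|---|---|---|
| 8 measures, 4 visits | 4 × 8 × 4 = 128 | 6.4 | 99.9% |
| 9 measures, 4 visits | 4 × 9 × 4 = 144 | 7.2 | 99.9% |
| 8 measures, 1 visit | 4 × 8 = 32 | 1.6 | 81% |
| 1 measure, 1 visit | 4 | 0.2 | 18.5% |

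The measures are not independent. With 128 tests, 60 patients in total and a pairwise correlation among outcomes of 0.5 or 0.8, simulation gives about 95% or 72% for at least one; the expected number stays near 6.4.

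Two features of the measures matter here. The section PROMs says WOMAC will be derived from KOOS, so one chance KOOS association can reappear as apparent replication. The MVIC section divides force by body weight, so its level is arithmetically linked to BMI whatever the treatment does.

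**The case against.** The strongest reply is that the article never claims these correlations will show who does better with fat than with PRP. The covariates enter as possible confounders, the between-group comparison is the stated main purpose, and the search is one clause about a further analysis. Asking whether BMI or grade relates to outcome is a legitimate prognostic question. The wording is loose, may simply mean associations, and a fuller plan that is not shown could specify interactions and multiplicity control.

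Much of this stands:

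- A reader might infer that the search **will** yield false predictors. The article does not support that certainty. The chance of at least one false positive runs from 18.5% to 99.9%, depending on choices it does not fix.
- A reader might infer that the results are meant to steer patients to one treatment. No passage says so; the wording only invites that reading.
- A reader might infer that factors significant in one arm only will be presented as selective effects. That requires a by-arm comparison, which the article does not plan.
- Multiplicity is a separate problem. Interaction terms alone do not reduce the number of tests; restricting the outcome and visit does.

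What does not stand is that this is merely missing detail. The article names a method, correlation; a target, the effectiveness of treatment; and an open scope. Followed as written, the method cannot address effect modification, whether pooled or by arm.

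**Conclusion.** The point holds in limited form. The stated correlations show prognosis only and cannot tell whether the fat-versus-PRP difference depends on BMI, age, sex or OA grade. With a purely prognostic factor (r = 0.3) and 20 to 50 per arm, the pooled correlation would be significant in about 47% to 86% of trials, against about 5% for the interaction test. An unrestricted search would give about 6 to 7 chance findings if no association exists.

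The conclusion about what a correlation measures needs no assumption beyond each patient receiving one treatment. The percentages rest on assumed sample sizes and correlations, and the 6 to 7 on testing every factor, measure and visit once. The prognostic scenario and the all-null scenario are alternatives and should not be added together.

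This is a secondary analysis and does not bias the main comparison. It is still worth correcting, because a better method is available on the same data.

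**What to change.** Reword the covariate analysis before any results are compared by arm:

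1. For any claim about differential benefit, replace the correlations with treatment-by-covariate interaction terms for the four named factors, with BMI and age kept continuous.
2. Fit them for one outcome at one time point, named in advance by the sponsor for this analysis, in a model adjusted for the baseline value of that outcome. This restriction brings the search from 128 to 144 tests down to 4 (4 × 0.05 = 0.2 expected chance findings).
3. Report each interaction estimate with its 95% confidence interval and label the analysis exploratory.
4. State what effectiveness means. Call any plain correlation that remains prognostic only, and do not compare significance between arms.

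**Cost.** No new data are needed. It is slightly more than a change of words, because the article currently names no main outcome, main time point or baseline-adjusted model, so the sponsor must choose these for this analysis. The interaction estimates will be imprecise in a small trial (15% to 33% power in the modest case above), so a non-significant interaction must not be read as evidence of a uniform effect.

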## Design

This is a prospective, randomized, controlled study. The purpose of this study is to assess functional and clinical changes among patients with symptomatic knee OA treated with intra-articular injections of autologous adipose tissue or PRP and to compare the efficacy of both therapeutic methods. We hypothesize that adipose tissue injections will improve patients’ quality of life and functional status and will decrease pain level significantly more than PRP injections. In addition to the functional tests and muscle strength measurement, the patient reported outcome measures (PROMs) of the knee joint function and quality of life will be used to assess each participant.

The study design meets CONSORT, MIBO and SPIRIT guidelines.

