## Discussion

This study protocol has several strengths and weaknesses. Undoubtedly one of strongest point of this study is wide, multidimensional functional assessment, which will give a large amount of objective data. To our knowledge, this research is the first one which includes the battery of functional tests and MVIC as an outcome measurement tool. This study will use 4 questionnaires, including WOMAC, which is described by physicians as a gold standard for assessing the effectiveness of knee OA treatment [45, 52].

On the other hand this study has several limitations. Primarily - the lack of blinding and we consider this as a risk of both, subject and investigator bias. Next and equally important limitation is a small size of the study. Furthermore, autologous fat tissue procedure is definitely more invasive and more stressful for the patients than PRP procedure. Hence, taking all into consideration, to adopt autologous fat tissue as a knee OA therapy, based on the future results, we have to detect definite, statistically significant and clinically noticeable difference.

Our PRP procedure gives us the possibility to examine the patient and assess the reaction to intra- articular injection 3 times (3 injections) in 7 day interval. These visits are often associated with physical therapy, which consists of manual therapy and individualized exercise program. Autologous fat tissue procedure does not give us such a possibility. The doctor and physiotherapist see the patient on the day of the surgery and 2 weeks after, during a control visit, which is also associated with physical therapy. Thus, there are some discrepancies between the two procedures at the beginning of the treatment process.

It has been proven that intra- articular injection of autologous fat tissue or PRP is a safety treatment option of knee OA [46, 47]. The most common complications after the intra- articular injection are pain and swelling of treated knee, but this improve after cold compression and NSAIDs. Also there were no cancer incidents reported after autologous fat tissue or PRP implantation [47].

Subject recruitment has started after we received Bioethical Committee approval.

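### The main purpose is a comparison of every outcome at every visit against one p < 0.05 threshold, with no primary outcome, primary visit or decision rule, so the overall false-positive rate is not controlled

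*Protocol article*

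**What the plan says.** The statistical part of the protocol article (Ethics, data management and statistical analysis) defines the aim of the analysis: "At every time point the results will be compared between treatment and control group, what is main purpose of this study". It continues: "The results obtained in each questionnaire, functional test and MVIC will create the effect across all time points". The only criterion given reads, for the p-value: "value of < 0.05 will be considered statistically significant".

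Outcomes measurement and Table 1 fix the scope. On visits: "Patients will be assessed five times: before treatment and 1, 3, 6 and 12 months after the treatment". On instruments: "The PROMs consist of the four questionnaires" (KOOS, IKDC 2000, WOMAC, EQ-5D-5L), and "three functional tests will be performed to assess" function (TUG, 5xSTS, 10mWT). MVIC is added for knee flexors and extensors. Every instrument is scheduled at every visit.

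Two other sections say what the trial hopes to conclude. Design hypothesises that fat tissue will do better on quality of life and functional status, and that it "will decrease pain level significantly more than PRP injections". The Discussion sets a condition for adopting fat tissue: "we have to detect definite, statistically significant and clinically noticeable difference". Neither names an instrument, a visit or a size of difference.

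**The concern.** The article does more than leave a primary endpoint unmentioned. It says what the main purpose is, and that purpose is the whole grid of outcomes by visits, all with equal standing and all judged against the same threshold. A later analysis plan that singled out one comparison would have to depart from this sentence.

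The hypothesis covers three domains, and the adoption condition asks for a difference that is both significant and clinically relevant. With no outcome, visit or rule attached, a reader of the results could not tell whether one significant cell out of more than thirty supports either. The Discussion itself calls the fat tissue procedure more invasive and more stressful, and describes the study as small and lacking blinding. A chance finding could therefore carry real weight.

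**Working it through.** **Plan's own figure.** The article states no family-wise error rate, so there is none to reproduce.

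**Number of comparisons.** Four questionnaires + three functional tests + MVIC = 8 measures. Over four post-treatment visits, 8 × 4 = 32. With MVIC flexors and extensors separate, 9 × 4 = 36. This counts one score per questionnaire; separate subscales would add tests.

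**Threshold.** 0.05 per comparison. Sidedness is not stated; two-sided is assumed, so the critical value is |z| > 1.96.

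**Independent tests, no true difference.** The chance of at least one false positive is 1 − 0.95^m:
- m = 32: 1 − 0.95^32 = 80.6%
- m = 36: 1 − 0.95^36 = 84.2%

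In the direction of fat tissue only, 1 − 0.975^m gives 55.5% (m = 32) and 59.8% (m = 36).

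**Correlated tests.** The measures come from the same patients over time, so independence overstates the rate. The article gives no correlations; those below are assumptions. Test statistics were simulated as multivariate normal under no true difference (at least 200,000 draws per scenario), with a common correlation between measures and a common correlation between visits. The result is the share of draws with at least one |z| > 1.96. The section PROMs says WOMAC is computed from KOOS, so each scenario was repeated with that pair set at r = 0.95 (also assumed).

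| Between measures / between visits | 32 tests | 32 tests, KOOS–WOMAC 0.95 | 36 tests | 36 tests, KOOS–WOMAC 0.95 |
|---|---|---|---|---|
| 0.3 / 0.5 | 69% | 66% | 73% | 70% |
| 0.5 / 0.6 | 58% | 56% | 61% | 59% |
| 0.7 / 0.7 | 43% | 42% | 45% | 44% |

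For a false result favouring fat tissue only (z > 1.96 in that direction), the same scenarios run from about 42% (0.3/0.5, 36 tests) down to about 21% (0.7/0.7, 32 tests with the KOOS–WOMAC pair at 0.95).

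**Reference points.** One outcome at one visit gives 5% in either direction and 2.5% in one. One outcome at all four visits, if independent, gives 1 − 0.95^4 = 18.6%. A Bonferroni limit over 32 tests would be 0.05/32 ≈ 0.0016.

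**The case against.** Several points against a harsher version of this criticism are sound.

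- *A reader might infer that any single p < 0.05 establishes superiority.* The article does not say so. It defines when a result is called significant, not what follows from it. The percentages above are therefore conditional on that reading. If the hypothesis were taken to require success on quality of life, function and pain together, error would not inflate across those three domains, although the choice of measure and visit within each would stay open. The text fixes neither reading.
- *A reader might infer that a false claim is more likely than not.* This holds under weak to moderate correlation but fails at 0.7/0.7 (42% to 45%). For a false result favouring fat tissue alone it fails in every correlated scenario examined.
- *A reader might infer that the p < 0.05 criterion is irrelevant to the trial's own aims.* It does serve the significance half of the adoption condition. The clinical half is a further hurdle that could screen out some chance findings, but with no threshold or outcome attached it gives no error control that can be quantified.
- *A reader might infer that the key outcome will be picked after the data are seen.* The article says only that recruitment began after ethics approval. The repeated interim look it describes concerns demographic balance.
- *The sentence on an effect across all time points might mean a longitudinal analysis per outcome.* It might, and that would cut the number of key tests. But it names no single test and does not withdraw the visit-by-visit comparison.
- *Multiplicity methods and a minimal important difference are often left to a full protocol or analysis plan.* True, and their absence alone would be no finding. What stands is that the article positively makes all comparisons the main purpose.

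**Conclusion.** The point holds in this form: the article makes 32 to 36 comparisons jointly the main purpose, under one 0.05 threshold, with no primary outcome, primary visit or decision rule. The hypothesis and the adoption condition do not say which result would satisfy them.

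If any one significant result were taken as a difference, the false-positive rate in either direction would be about 42% to 73% under the assumed correlations, and higher if the tests were independent. The exact value depends on correlations the article does not give and on one score per questionnaire. The conclusion does not: in every scenario examined, including a nearly redundant KOOS–WOMAC pair, the rate is at least eight times the nominal 5% (42/5 = 8.4). The case rests on that inflation and the missing decision rule, not on whether the figure passes one half.

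**What to change.** By dated amendment, before any outcome is compared by arm:

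1. Replace the sentence defining the main purpose with one named primary outcome at one named visit, tested at two-sided 0.05. The investigators should choose it from those already scheduled; a KOOS or WOMAC pain score at 12 months is one example.
2. Make all other measures and visits secondary. Either test them in a fixed order or with Holm adjustment, or report them as estimates with 95% confidence intervals and no significance claims.
3. State the difference on the primary score that counts as clinically relevant, and base the Discussion's adoption statement on the primary confidence interval against that value.
4. Say what the sentence on the effect across all time points means. If a longitudinal model is intended, give it a defined place among the secondary analyses or as the source of the primary estimate.

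The cost is the amendment itself and bringing the registry entry into line if it differs (the entry was not available here). No extra visits or measurements are needed. The real downside is that fewer results can be called significant.

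### The across-time effect is worded over all time points, which read literally include the pre-treatment visit; it should be limited to months 1, 3, 6 and 12, with the month-0 value as a covariate

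*Protocol article*

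**What the plan says.** The section on ethics, data management and statistical analysis makes two statements about how the arms are compared. The first concerns single visits: "At every time point the results will be compared between treatment and control group, what is main purpose of this study". The second concerns the whole follow-up: "The results obtained in each questionnaire, functional test and MVIC will create the effect across all time points".

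The outcomes section sets the schedule: "Patients will be assessed five times: before treatment and 1, 3, 6 and 12 months after the treatment". Table 1 marks every questionnaire, functional test and strength measurement at month 0 as well as at the four later visits.

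The only baseline variables given a possible analytic role are patient characteristics: "At the start we consider BMI, age, sex and knee OA grade as a possible confounders". The pre-treatment value of the outcome is not among them. The analysis set is restricted to complete attenders: "Only patients who attended all of visits, performed each functional test and MVIC and fulfilled each questionnaire will be included in the analysis".

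**The concern.** At month 0 nobody has been treated. In a randomized comparison the expected difference between arms is zero there, and any observed gap is chance. A summary that counts month 0 as one of the visits mixes a known zero with four post-treatment differences. It also treats part of the chance gap as if it were treatment effect.

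The across-time effect would give one answer per outcome over the 12 months. The Discussion says that adopting the more invasive fat procedure would need a difference that is both statistically significant and clinically noticeable. A summary pulled toward zero works against both criteria. The authors also write "Next and equally important limitation is a small size of the study", so there is little power to spare and chance baseline gaps are to be expected.

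**Working it through.** The article gives no sample size, effect size, standard deviation or correlation, so there is no stated figure to reproduce. The check asks what including month 0 would do under each plausible estimator.

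**Inputs from the protocol**
- Five visits: month 0, then months 1, 3, 6 and 12.
- Every analysed patient has all five visits, so the data are balanced. The group main effect of a five-visit analysis then equals the equal-weight average of the five visit differences.
- Significance level 0.05; sidedness is not stated.

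**Assumptions**
- Standard deviation 1 at every visit and a constant between-visit correlation rho of 0.3, 0.5 or 0.7.
- Two-sided testing, and the effect sizes stated below.

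**1. Dilution**

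Let the post-treatment differences be d1 to d4, and let the expected month-0 difference be 0.
- Five-visit mean: (0 + d1 + d2 + d3 + d4)/5. Four-visit mean: (d1 + d2 + d3 + d4)/4. The ratio is 4/5 for any profile. For (1, 1, 1, 1) the results are 0.80 and 1.00; for (0, 0.5, 1, 1) they are 0.50 and 0.625.
- Trapezoid area over 0 to 12 months, divided by 12, for a constant difference of 1: (0.5 x 1 + 1 x 2 + 1 x 3 + 1 x 6)/12 = 11.5/12 = 0.958. The loss is about 4%.
- Change from baseline averaged over the four later visits: no dilution.

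**2. Share of a chance month-0 gap carried into the effect**
- Five-visit mean: (1 + 4 rho)/5 = 0.44, 0.60, 0.76.
- Four-visit mean without baseline adjustment: rho = 0.30, 0.50, 0.70.
- Added by counting month 0: (1 - rho)/5 = 0.14, 0.10, 0.06.
- Four-visit mean with baseline as covariate: 0.

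**3. Variance per patient**

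| Estimator | Formula | rho 0.3 | rho 0.5 | rho 0.7 |
|---|---|---|---|---|
| Five-visit mean | (1 + 4 rho)/5 | 0.44 | 0.60 | 0.76 |
| Five-visit mean, rescaled to the full effect | above / 0.64 | 0.69 | 0.94 | 1.19 |
| Four-visit mean, unadjusted | (1 + 3 rho)/4 | 0.475 | 0.625 | 0.775 |
| Four-visit mean of change | (1 + 3 rho)/4 + 1 - 2 rho | 0.875 | 0.625 | 0.375 |
| Four-visit mean, baseline covariate | (1 + 3 rho)/4 - rho^2 | 0.385 | 0.375 | 0.285 |

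Before rescaling, dropping month 0 does not lower the variance (0.60 against 0.625 at rho 0.5). What it removes is the attenuation. The reduction in variance comes from the covariate. On the rescaled line both steps count. At rho 0.5, dropping month 0 multiplies the variance by 0.625/0.9375 = 0.67, and the covariate multiplies it by a further 0.375/0.625 = 0.60. At rho 0.7 the covariate dominates; at rho 0.3 dropping month 0 contributes more.

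**4. Illustration only**

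Patients per arm for 80% power at an assumed difference of 0.5 SD, for rho 0.3, 0.5 and 0.7:
- five-visit mean: 44, 59, 75
- unadjusted four-visit mean: 30, 40, 49
- baseline-adjusted four-visit mean: 25, 24, 18

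**The case against.** The strongest reply is that the article names no estimator. It does not mention a mean, equal weights, raw scores or a group main effect. The Design section frames the aim as assessing changes, and on that reading month 0 is simply the reference from which change is measured. The term time point occurs only in the statistical section and is undefined there; the outcomes section speaks of assessments, and Table 1 of visits and months. Model form, visit weights and the role of baseline are also details that a condensed article commonly leaves to a fuller document.

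Much of this stands. A reader might infer that the planned effect is shrunk by one fifth. The documents do not support that as a fact: it follows only for an equal-weight average or a group main effect. A reader might also infer that the effect takes in the whole of any baseline gap. It would take in part, and most of that part arises because no baseline adjustment is stated, not because month 0 is counted. Nor is the main comparison harmed: the differences at months 1, 3, 6 and 12 are undiluted on any reading, and a between-arm look at month 0 says nothing about efficacy but does them no damage.

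What does not stand is that this is only missing detail. The sentence does say which visits form the effect, namely all of them, and the schedule puts a pre-treatment visit among them. An analysis plan that used only the later visits would depart from the sentence as written.

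**Conclusion.** The point holds as a defect of wording with a conditional consequence. Read literally, month 0 enters the across-time effect, and the baseline outcome value has no stated role. If the effect is an equal-weight five-visit average or group main effect, it is 20% smaller than the mean post-treatment difference, and at rho 0.3 to 0.7 it carries 44% to 76% of a chance baseline gap. Counting month 0 accounts for only 14 to 6 percentage points of that share. Under a time-weighted area the loss is about 4% for a constant difference, and under change from baseline there is none.

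The 20% is arithmetic on the protocol's five visits and needs no assumption beyond the estimator. The shares, variances and patient numbers rest on equal variances, a constant correlation and an assumed effect. They illustrate the direction and rough size and do not describe this trial's power. The documents do not show that the authors intend a plain five-visit average.

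**What to change.** Replace the sentence on the across-time effect with wording such as: for each outcome, the overall effect is the fat-minus-PRP difference averaged over months 1, 3, 6 and 12, estimated from a repeated-measures model with the month-0 value of that outcome as a covariate; month 0 is not an outcome visit. Add that efficacy comparisons at every time point mean those four post-treatment visits.

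The cost is a sentence or two of analysis text. No data, visits or patients are added, because every outcome is already measured at month 0. If the authors already meant this, the edit only records it. Under the assumed correlations the baseline-adjusted four-visit mean also has a smaller variance than change from baseline (0.385, 0.375, 0.285 against 0.875, 0.625, 0.375), so the edit is worthwhile even if a change score was intended.
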